## Abstract

**Background:**

After curative treatment for breast cancer women frequently attend scheduled follow-up examinations. Usually the follow-up is most frequent in the first 2–3 years (2–4 times a year); thereafter the frequency is reduced to once a year in most countries. Its main aim is to detect local disease recurrence, or a second primary breast cancer, but also to provide information and psychosocial support. However, the cost-effectiveness of these frequent visits is under much debate, leading to a search for less intensive and more cost-effective follow-up strategies.

In this paper the design of the MaCare trial is described. This trial compares the cost-effectiveness of four follow-up strategies for curatively treated breast cancer patients. We investigate the costs and effects of nurse-led telephone follow-up and a short educational group programme.

**Methods/design:**

The MaCare trial is a multi centre randomised clinical trial in which 320 breast cancer patients are randomised into four follow-up strategies, focussed on the first 18 months after treatment: 1) standard follow-up; 2) nurse-led telephone follow-up; 3) arm 1 with the educational group programme; 4) arm 2 with the educational group programme. Data is collected at baseline and 3, 6, 12 and 18 months after treatment. The primary endpoint of the trial is cancer-specific quality of life as measured by the global health/QoL scale of the EORTC QLQ-C30. Secondary outcomes are perceived feelings of control, anxiety, patients' satisfaction with follow-up and costs. A cost-effectiveness analysis will be performed from a societal perspective.

**Discussion:**

Reduced follow-up strategies for breast cancer have not yet been widely applied in clinical practice. Improvement of psychosocial support and information to patients could lead to a better acceptance of reduced follow-up. The MaCare trial combines a reduced follow-up strategy with additional psychosocial support. Less frequent follow-up can reduce the burden on medical specialists and costs. The educational group programme can improve QoL of patients, but also less frequent follow-up can improve QoL by reducing the anxiety experienced for each follow-up visit. Results of the trial will provide knowledge on both costs and psychosocial aspects regarding follow-up and are expected in 2009.

## Background

With an estimated 1.15 million new cases worldwide each year, breast cancer is by far the most frequent cancer in women. Because of its high incidence and relatively good prognosis, breast cancer is also the most prevalent cancer in the world today [1]. After curative treatment for breast cancer women frequently attend scheduled follow-up examinations. Usually the follow-up is most frequent in the first 2–3 years (2–4 times a year); thereafter the frequency is reduced to once a year in most countries. The main objective of these examinations is to detect local disease recurrence or a second primary breast cancer in an early stage, hoping that this may increase the chances of cure. Follow-up should also provide information and psychological support. Another aim is to collect data on late effects of surgery, radiotherapy and chemotherapy for audit or research and to provide feedback to physicians [2,3]. However, there is much debate whether the objectives of breast cancer follow-up are adequately met in current practice [4,5]. Schapira (1993) reported that the early frequent outpatient clinic visits with only physical examination and an annual mammography do not improve early detection of recurrence or overall survival [6]. Since then, several studies have investigated the effect of the frequency [7] and intensity [8,9] of follow-up on overall survival, without finding evidence supporting the necessity of frequent or intensive follow-up. Furthermore, instead of providing psychosocial support, it has been demonstrated that the outpatient clinic visit may induce anxiety because of the risk of detecting tumour relapse [10,11].

Although the current frequent follow-up strategies thus seem to miss their most important goals, they do depend heavily on expensive and scarce specialised knowledge for routine history taking and physical examination. Financial constraints have forced oncologists and policy makers to search for alternative and cost-effective follow-up strategies. Studies on follow-up by the general practitioner, patient-initiated or nurse-led follow-up or contact by telephone showed no difference in time to detection of recurrence or patients perceived quality of life (QoL) [12-16]. Nevertheless, these reduced strategies have not yet been widely accepted and applied in clinical practice. This may on the one hand be ascribed to the perception of many medical specialists that most patients need reassurance and psychosocial support, and on the other hand to the false expectations of many patients that frequent follow-up will result in a better overall survival [17]. Improvement of the psychosocial support and education of the patients may lead to a better acceptance of both patients and medical specialists of a reduced follow-up policy. A number of studies have been performed using various group intervention formats for breast cancer patients to provide psychosocial support. However, most interventions mainly focussed on intensive psychological support (10 sessions or more), showing varying results and often high refusal rates [18].

No trials have been performed that combine a reduced follow-up policy in the first 2 years with an acceptable strategy to provide information and education. For this reason, two interventions for early breast cancer follow-up were developed for the study that is discussed in this paper; nurse-led telephone follow-up and a short educational group programme (EGP). The primary aim of the so-called MaCare trial (Mamma carcinoma and afterCare) is to investigate the impact of these interventions on cancer-specific QoL and costs and thus to determine which of these follow-up strategies is the most cost-effective. This paper reports on the methodological design of the trial as well as the contents of the interventions and the economic evaluation.

## Methods/Design

### Study design

The MaCare trial is a multi centre randomised trial, in which breast cancer patients who are treated with curative intent are randomised between four follow-up strategies (see figure 1):

1) Follow-up as usual; 5 outpatient clinic visits in the first 18 months (at 3, 6, 9, 12, and 18 months), with a mammography at one year.

2) Nurse-led telephone follow-up; a mammography at one year combined with an outpatient clinic visit, and telephone interviews by a breast care nurse (BCN) or nurse practitioner (NP) at the same time points as during the usual follow-up (i.e. 3, 6, 9 and 18 months).

3) Similar to arm 1, combined with the EGP.

4) Similar to arm 2, combined with the EGP.

After 18 months patients return to the current follow-up strategy, i.e. follow-up once a year.

### Setting

The trial is carried out in seven hospitals and two radiotherapy clinics located in the south of The Netherlands. Medical specialists working in the participating centres have been recruiting patients since July 2005 and will continue recruitment until approximately September 2007. Follow-up as usual takes place in the hospital where surgery and chemotherapy were performed, alternating between the surgeon, medical oncologist and radiation oncologist. The telephone follow-up is performed by the nurse practitioner (NP) or breast care nurse (BCN) working at this hospital. An NP is a registered nurse who has acquired (at masters level) the expert knowledge base, complex decision-making skills and clinical competencies for expanded practice. The BCN is a qualified nurse who has had specialist training in breast care and who guides the patient throughout treatment. In this paper the term BCN is used and refers to both types of nurses. The EGP is held at cancer information centres. These centres are specialised in providing support to (ex-)cancer patients and their relatives through education and organising activities. Selecting participants from multiple centres and locations in the Netherlands allows us to include a representative selection of breast cancer patients. Participation is voluntary and after written informed consent is obtained. Prior to the start of the study the protocol was approved by the Medical Ethical Committee of MAASTRO Clinic. Furthermore, all participating centres signed a declaration on local feasibility before inclusion of their first patient, according to the Dutch law and regulations.

### Study population

#### Selection of participants

Patients are recruited and included within 6 weeks after completion of treatment with curative intent by the medical specialist of the last treatment modality. Eligibility criteria are summed up in table 1. If eligible, the medical specialist introduces the MaCare trial to the patient and gives her a detailed information sheet. Within two weeks, the research assistant contacts the patient to explain the aim and implications of the trial again. Eligibility criteria are checked once more and the research assistant asks whether the patient wants to participate.

#### Non-participants

Patients who are eligible for inclusion but not interested in participation are asked to fill out the same baseline questionnaires (see outcome parameters) as participants. By assessing whether there are differences between participants and non-participants the external validity of the study results can be determined.

#### Sample size calculations

The primary outcome measure is cancer specific QoL at 12 months after randomisation, measured by the global health/QoL scale of the EORTC QLQ-C30. A baseline score of 64 with a standard deviation of 17 [19,20] is considered as a starting point. In an analysis of the clinical significance of changes in QoL, Osoba et al (1998) showed that patients judge a change between 5–10 to be small, between 10–20 to be moderate, and more than 20 to be large [21]. Consequently, we considered a change smaller than 5 points to be no change. To show that QoL of patients in arms 2 and 4 (telephone follow-up) is at least similar to patients in arm 1 and 3 (usual follow-up) with a power of 80% and a significance level of 0.05, the required number of patients per group is 80. With these 320 patients an improvement in QoL, by adding the EGP compared to no EGP, of 10 points with a power of 0.95 and a significance level smaller than 0.01 can be detected. A dropout rate of 10% is accounted for in these calculations.

### Randomisation

After written informed consent and completion of the baseline questionnaire, randomisation by minimisation is performed by the Comprehensive Cancer Centre Limburg. Patients are pre-stratified by treatment modalities and hospital. After randomisation, the research assistant contacts the patient and informs her about the assigned study-arm, thus whether she will receive standard or telephone follow-up and whether she will be invited to join the EGP.

### Interventions

#### Usual care

The first study arm, the standard arm, consists of follow-up as described in the Dutch guidelines. After treatment, the patient has an outpatient clinic visit with the medical specialist or BCN every 3 months during the first year, every 6 months during the second year, and thereafter once a year until at least 5 years. Mammography is taken once a year.

#### Nurse-led telephone follow-up

In study arms 2 and 4 a mammography is taken once a year, which is combined with a visit to the medical oncologist, the surgeon, BCN or the radiation oncologist. At the other regular follow-up times (i.e. at 3, 6, 9, and 18 months), the BCN has a telephone interview with the patient. The telephone interview is done by open discussion and a semi structured questionnaire, including screening for physical – especially loco regional – and psychosocial symptoms, and compliance to hormonal therapy. Data on the side effects of treatment are also collected during the interview. Furthermore, the BCN informs about general well being of the patient, her family-life, relationships and work reintegration. When the patient does not feel reassured an additional appointment is made for her to come to the hospital. The telephone follow-up is mainly meant to reduce the workload of medical specialists, with possible reduction of costs, but could also influence QoL as a result of a reduction of stressful visits to the outpatient clinic [11]. To adequately perform the telephone interview, all participating BCNs attained a training, specifically developed for this study. In this training nurses are informed on the most recent developments in breast cancer treatment and follow-up, develop a semi-structured questionnaire for support during the interview, and practice their telephone communication skills with a breast cancer patient.

#### Educational Group Programme

In arms 3 and 4 of the study, the patient and their partner (or close friend or family member) are invited to participate in the Educational Group Programme (EGP) within three months after treatment. The basic theory underlying the EGP is the transaction process theory of stress [22]. The group-format programme focuses on the first two stages of the transaction process theory of stress, the primary and secondary appraisal. The EGP therefore consists of two interactive group sessions of 2,5 hours of patient education. In the first session, which addresses the primary appraisal, a BCN provides information on possible side effects of the different treatments and issues such as prostheses, exhaustion, hereditary issues and financial consequences. Also, signs and symptoms of recurrences are discussed. A health care psychologist concentrates on psychological consequences, like anxiety, depression and changed family role patterns. The second session focuses on the second appraisal, i.e. information is provided on possible coping strategies and actions that could be undertaken when symptoms occur. Furthermore, information on the various health care workers and additional interventions is given. Discussions are stimulated by the speakers, addressing issues such as how to deal with anxiety, mood changes and changes in relationships. In this way, patients and their partners are stimulated to be alert to symptoms, and to enhance self-efficacy in adopting one of the proposed actions or coping strategies. It is expected that this will lead to a better QoL. During the second session a volunteer from the Dutch Breast Cancer Association presents regional activities available for participants. The EGP is completed with a relaxation exercise. After the two sessions, participants receive a small booklet encompassing the topics discussed in the programme. The BCN and health care psychologist use standardised presentations, so that the EGPs given during the time of this study are as similar as possible. Furthermore, by using standard presentations, different teams can lead the EGP and the programme will be easily transferable to other settings.

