### Statistical analyses

To evaluate differences in QoL outcome between the study arms, the data will be analysed using a multivariate linear regression model. In this model both the EGP factor and the telephone factor will be taken into account. In addition, variables such as age, hospital treatment, and experienced support of a partner, will be brought into the model. The procedure will be performed 4 times as QoL is assessed at 3, 6, 12 and 18 months. Differences in satisfaction with care, perceived behavioural control and anxiety will be analysed in the same way. Participation at group meetings will be analysed using logistic regression models. Differences in medical consumption will be evaluated using a multivariate linear regression model. Subgroup analysis will be performed to identify specific patient characteristics that could predict the optimal follow-up strategy for the individual patient. Data will be analysed according to the intention-to-treat principle.

The number of recurrences is expected to be very low with a follow-up of 18 months [28]. Statistical analysis of the difference in time-to-detection per group will therefore be limited to descriptive statistics.

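### The stated regression has no term for EGP group, so if outcomes are correlated within groups the EGP confidence intervals and p-values will be too optimistic

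*Protocol article*

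**What the plan says.** All points are from the protocol article.

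- **Educational Group Programme.** Women in arms 3 and 4 are invited to the programme within three months after treatment. Its form is: "The EGP therefore consists of two interactive group sessions of 2,5 hours of patient education". A breast care nurse and a psychologist lead it, and discussion among participants is encouraged. The presentations are standardised to keep the sessions alike. The section adds that, because of this, "different teams can lead the EGP and the programme will be easily transferable to other settings".
- **Statistical analyses.** For QoL, "the data will be analysed using a multivariate linear regression model". The model holds both factors and covariates such as age, hospital treatment and partner support. It is fitted separately at 3, 6, 12 and 18 months. Satisfaction, perceived control and anxiety are handled the same way, by intention to treat. EGP group is not mentioned.
- **Sample size calculations.** The endpoint is fixed thus: "The primary outcome measure is cancer specific QoL at 12 months after randomisation". The inputs are "A baseline score of 64 with a standard deviation of 17", a limit for the telephone comparison ("we considered a change smaller than 5 points to be no change") and 10% dropout. For the EGP, the section says that an improvement "of 10 points with a power of 0.95 and a significance level smaller than 0.01 can be detected".

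**The concern.** Women in one EGP group share the discussion, the other participants, the nurse, the psychologist and the occasion. Their later scores may therefore resemble each other more than those of women from different groups. Arms 1 and 2 have no such groups, so the design is partially nested: clustering can arise on one side of the EGP contrast only.

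A linear regression with independent residuals counts every woman in the EGP arms as a separate piece of information. With positive within-group correlation that overstates the information, and a chance run of good groups can pass for a programme effect. The EGP is one of the trial's two randomised factors and is expected to raise the primary outcome, so the precision of this contrast bears on a main conclusion. The estimate itself is not biased by this; its standard error is what suffers.

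**Working it through.** **1. Do the plan's own figures assume independent patients?**

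Inputs from the Sample size calculations section: SD 17, margin 5, "with a power of 80% and a significance level of 0.05, the required number of patients per group is 80", 10% dropout. I take the 0.05 as one-sided, since the section does not say.

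- Telephone factor, per level: n = 2·[17·(1.645 + 0.842)/5]² ≈ 143. Dividing by 0.9 gives 159 per level, or 79.5 per arm. This reproduces the stated 80. (One-sided 0.025 gives 182, then 203 after dropout, or 101.5 per arm, which does not match.)
- EGP factor with 160·0.9 = 144 per level: SE = 17·sqrt(2/144) = 2.003. Power for 10 points at two-sided 0.01 is Φ(10/2.003 − 2.576) = 0.992, above the stated 0.95.

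Both figures come out of formulas for independent patients, with no design effect.

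**2. Effect of partial nesting on the EGP standard error**

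With groups of size m and intraclass correlation ICC, the variance on the EGP side is multiplied by 1 + (m−1)·ICC and the other side is unchanged. For the contrast:

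- variance ratio R = 1 + (m−1)·ICC/2
- true SE = sqrt(R) × reported SE
- true type I error = 2·[1 − Φ(z/sqrt(R))], with z = 1.960 for a nominal 5% and 2.576 for 1%
- power with the correct SE = Φ(10/(2.003·sqrt(R)) − 2.576)

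The documents give neither m nor ICC, so both are assumptions. For m = 10 and full attendance:

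| ICC | R | sqrt(R) | True error, nominal 5% | True error, nominal 1% | Power, 10 points at 0.01 |
|---|---|---|---|---|---|
| 0 | 1.000 | 1.000 | 5.0% | 1.0% | 0.992 |
| 0.01 | 1.045 | 1.022 | 5.5% | 1.2% | 0.990 |
| 0.05 | 1.225 | 1.107 | 7.7% | 2.0% | 0.973 |
| 0.10 | 1.450 | 1.204 | 10.4% | 3.2% | 0.942 |

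Over m = 6 to 15 and ICC 0.01 to 0.10, the true error runs from 5.3% to 13.3% at nominal 5%, and from 1.1% to 4.8% at nominal 1%.

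**3. Check by simulation and allowance for non-attendance**

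Simulation with 20,000 trials per setting (m = 10, ICC 0.05, full attendance) gave 7.5% and 1.9%, in line with the formula. With 70% of EGP patients attending and the rest unclustered, it gave 6.6% and 1.6%. The formula with attendance built in agrees: R = 1 + 0.7·9·0.05/2 = 1.158, which gives 6.8% at nominal 5%.

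**4. Does the stated EGP power survive?**

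At two-sided 0.01 with the correct SE, power is 0.957 at m = 8 and ICC 0.10, and 0.957 at m = 15 and ICC 0.05. It falls below 0.95 at m = 10 and ICC 0.10 (0.942), at m = 12 and ICC 0.10 (0.924), and at m = 20 and ICC 0.05 (0.938). Elsewhere in the plausible range the claim stands, because the telephone comparison set N and left the EGP contrast a large reserve.

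**The case against.** Five points can fairly be made against this.

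- **The correlation is assumed, not shown.** This stands. At ICC = 0 the level is held, and at ICC 0.01 the inflation is negligible. The point can only be conditional.
- **Exposure is short, standardised and distant from the endpoint.** The programme is five hours in total, within three months after treatment, and the primary outcome is at 12 months. This argues against the upper end of the ICC range. But standard presentations limit differences between leaders; they do not remove dependence that arises from group composition and from discussion, which the programme encourages. The sentence about different teams concerns transferability and does not say how many teams ran groups in this trial.
- **Attendance will be incomplete.** Women are invited, and participation is itself to be analysed. This reduces the inflation, as the 70% case shows, without removing it.
- **Standard error details may be in an analysis plan that is not shown.** This stands in part: the covariate list is open and the article does not say how standard errors are computed. But it does state the model, and followed as written that model has no group term. Group membership is also best captured when sessions are held, and a later plan may be unable to recover it.
- **Hospital adjustment may absorb the clustering.** Only partly. The sessions take place at cancer information centres, and no listed covariate identifies the group.

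A reader might go further and infer that the sample size or the EGP power claim is wrong. The documents do not support that: the claim fails only near ICC 0.10 with groups of about 10 or more, or near ICC 0.05 with groups of about 20. Nor do they show harm to the telephone comparison. That contrast is little affected if groups mix women from arms 3 and 4, and the article does not say whether they do.

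**Conclusion.** The point holds in conditional form and is confined to the confidence intervals and p-values of the EGP factor. For any positive within-group correlation, the stated regression understates the EGP standard error. Assuming groups of 10 and full attendance, the true SE is 1.02, 1.11 or 1.20 times the reported one for ICC 0.01, 0.05 or 0.10. A nominal 95% interval would then cover about 94.5%, 92.3% or 89.6% of the time (100% minus the error rates in the working). Incomplete attendance pulls these figures back towards nominal.

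It would be too strong to say that the significance level is not held as a matter of fact, because that depends on an ICC and a group size that the documents do not give. The same model is used for anxiety, perceived control and satisfaction, so the same caution applies there, but the documents give no basis for assuming the same ICC for each. The change is worth making because it is cheap and the EGP contrast is a main result.

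**What to change.** - Record for each attender which EGP group she joined and which team led it.
- Analyse the EGP effect on QoL and the other patient-reported outcomes with a partially nested mixed model. Use a random group effect in arms 3 and 4 only, treat non-attenders and all women in arms 1 and 2 as singletons, and use small-sample degrees of freedom. The EGP factor stays as randomised, so the analysis remains intention to treat.

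**Cost.** Group and team need to be noted on the attendance list, which the planned participation analysis needs in any case, and the model command changes. EGP intervals become slightly wider; if the ICC is near zero, little precision is lost. No change to the 320 patients is needed.
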